### Randomization, Allocation, Blinding, Patient Timeline, and Data Collection Methods

2.5

Randomization will be performed before each training protocol, taking into account the 3 different types of training protocols. The order in which the patient will perform the training protocol will be determined by a simple draw in an envelope containing 3 papers described as 1 series, 2 series, or 3 series. Therefore, if in the first session the patient draws the paper described as 1 series, in the following week this paper will be removed from the envelope and the same will draw 2 or 3 series, and so on.

In this way, all patients involved in the study will randomly perform the 3 types of protocols proposed in the study, and they will be their own controls. To avoid allocation bias, opaque sealed envelopes will be used, with sequential numbers on the outside of the envelope. This allocation will be made by Researcher B, who will not be involved in any other study procedures. Patients selected in the screening conducted by Researcher A who agree to participate in the research will be randomly assigned.

Regarding blinding, all assessments will be performed by Researcher A, who will not be involved in the interventions and will not participate in the delivery of the training protocol. Each patient will remain identified by numbers and not by name. In order not to compromise the blinding of the study, all patients will undergo the same assessment before and after the training session. Due to the nature of the proposed intervention (physical exercise), the therapist and patients will not be blinded to the intervention. Patients will be instructed not to disclose any information to other patients and/or researchers.

At the end of the T3 training protocol, with a 7‐day interval between these assessments, we will conduct T4, where each patient will be asked which training protocol they prefer. After T4, researcher D will tabulate the data, which will be delivered to researcher E, who will be responsible for the statistical analysis and who will not participate in the previous phases of the research (Figure 2).

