**FIGURE 3 pri70101-fig-0003:**
[figure not shown]
Proposed exercises.

The T1 assessment will be performed respecting a 7‐day interval after the T0 assessment. At this interval, the patient will return and we will perform the first training protocol drawn on that day (T1). In addition, we will collect the following variables: pain intensity and affect before and after training, total training volume, and subjective effort after training.

The T2 and T3 assessments will follow the same procedure as T1, with a 7‐day interval between each protocol (T1, T2 and T3), so that the patient will perform the other two training protocols. The protocol draw will take place on the respective days of each assessment (T2) and (T3). If the envelope of the protocol drawn has already been performed on previous days, the patient will be instructed to perform a new draw.

Finally, at the T4 assessment, one week after the T3 assessment, the patient will be asked by telephone by the same evaluator (T0 baseline) about his preference for the programs performed in the study (with 1, 2 or 3 sets), standardizing the same commands used in person throughout the study. The following is a description of the three types of training programs with different volumes. The only different training variable will be the number of sets in the three training protocols of the study (Table 1).

**TABLE 1 pri70101-tbl-0001:** Training protocol.

Training (protocol)	Exercise	Sets (*n*)	Repetitions (*n*)	Load (1RM)	Rest (minute)
1	1–4	1	10	60%	2
2		2			
3		3			

*Note:* 1RM: One‐repetition maximum test. Each patient will receive the exercise session individually, as each of the three training protocols has different volumes (i.e., 1, 2, or 3 sets), consequently, the durations will vary for each patient; and then the durations will be compared between the groups.

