### Pain Intensity

2.11

The intensity of widespread pain is assessed using the numerical pain rating scale, a self‐report instrument validated for Portuguese (Ferreira‐Valente et al. 2011). The Numeric Pain Scale has a sequence of numbers (from 0 to 10), where 0 represents “no pain” and 10 represents “the worst pain imaginable”. A reduction of 2 points in pain intensity is considered a minimal clinically important difference (Farrar et al. 2001). The numerical pain scale is answered by the patients at three time points: at the beginning, at the end, and 24 h after the end of each resistance training session.

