### Participant and Audience Engagement

2.16

Patients will not be involved in the design of the study, the formulation of the research question, or the development of recruitment procedures. At the end of the study, the results may be reported to the patients in the form of a presentation of the effects found on the variables studied. If superiority of one program over another is found, this will be reported to the research patients.

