### Statistical Methods

2.18

For the primary outcome (preference), the number of choices of the 3 types of training will be recorded as a percentage. For the analysis of the primary outcome, we will summarize the patient's preference in a contingency table, compare the proportions using the chi‐squared test, and finally verify the effect size of the observed differences. For the secondary outcomes, statistical analyses will be performed by a blind statistician using commercial software. The independent variables of group and time (T0, T1, T2, T3, T4) will be considered for each dependent variable: pain intensity, subjective effort, affect and satisfaction. The Kolmogorov–Smirnov test was used to verify the distribution of the data and the Levene test was used to analyze the homogeneity of variance.

A mixed design analysis of variance will be conducted for the primary and secondary outcomes with a normal distribution, with time as the within‐subject factor and group as the between‐subject factor. If the data are not normally distributed, the Friedman test is used. Time × group interactions and between‐ and within‐group differences were analyzed for all variables. Finally, the Bonferroni test is used in post hoc analyses to determine whether there are differences between‐groups at different intervention times. A 5% significance level and 95% confidence interval will be used for all statistical analyses.

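### Within-protocol changes in pain and affect are tested on an equal footing with the between-volume comparisons, although every session is exercise and such changes have no comparator

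*Protocol article*

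**What the plan says.** All references are to the protocol article.

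- **Analyses planned (2.18 Statistical Methods).** Alongside time × group interactions, between- and within-group "differences were analyzed for all variables". The post hoc Bonferroni test is used "to determine whether there are differences between‐groups at different intervention times". On the level: "A 5% significance level and 95% confidence interval will be used for all statistical analyses". Nothing ranks the within-group tests below the other two kinds.
- **Conditions (2.5 and 2.6).** "all patients involved in the study will randomly perform the 3 types of protocols proposed in the study, and they will be their own controls". Of the sessions, 2.6 says: "The only different training variable will be the number of sets in the three training protocols of the study". No exercise-free session is described.
- **Repeated ratings (2.11, 2.12 and Table 2).** For pain: "The numerical pain scale is answered by the patients at three time points: at the beginning, at the end, and 24 h after" each session. Affect is rated at the same three times. Table 2 shows perceived effort, training volume and cadence once per session.
- **Reporting (2.16).** "the results may be reported to the patients in the form of a presentation of the effects found on the variables studied". The sentence that follows adds that superiority of one program over another, if found, will also be reported to patients.

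**The concern.** In this crossover a woman is her own control for one number of sets against another. She is not her own control for exercise against no exercise. If pain falls from before to after a 1-set session, the fall may come from the session, from ordinary fluctuation over the day, from being asked again, or from regression to the mean. Nothing in the design separates these.

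The second difficulty is how such tests are read. With one within-protocol test for each of three volumes, a significant result for one and a non-significant result for another looks like a difference between volumes. It is not a test of one, and such splits are common when the volumes act identically. At stake is what the trial says about pain and affect, including what may be presented to patients.

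**Working it through.** **1. Which outcomes are affected.** A within-session change needs at least two ratings in a session. By Table 2 only pain and affect have them (before, after, 24 h). Perceived effort, volume and cadence have one value per session, and preference is asked once, at the end. So the point covers pain and affect only, although the plan's sentence speaks of all variables.

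**2. The plan's own figure.** 2.17 gives w = 0.8, α = 0.05, 25 degrees of freedom and 36 patients. λ = N × w² = 36 × 0.64 = 23.04, the critical value is 37.65, power is 0.804, and 36 is the smallest N that reaches 0.80. The figure reproduces. I use 36 below only as the number of women; the point does not depend on how it was derived.

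**3. Assumptions, none of them in the documents.** The true change is the same in all three protocols. The standardised change dz (mean change divided by the SD of change) is 0.2, 0.33 or 0.5. The correlation between a woman's changes in different sessions is 0 to 0.7. Tests are two-sided at 5%.

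**4. Independent sessions, by formula.** The power p of one within-protocol paired t test comes from the non-central t distribution with 35 degrees of freedom and non-centrality dz × √36 = 6 × dz. The chance that the three verdicts are mixed (at least one significant, at least one not) is 1 − p³ − (1 − p)³.

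- dz = 0.2: p = 0.215, mixed 0.506
- dz = 0.33: p = 0.486, mixed 0.749
- dz = 0.5: p = 0.831, mixed 0.422

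**5. Correlated sessions, by simulation.** There were 20,000 trials per cell, with normal changes and n = 36. Chance of mixed verdicts among the three protocols:

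| Correlation | dz = 0.2 | dz = 0.33 | dz = 0.5 |
|---|---|---|---|
| 0 | 51% | 75% | 42% |
| 0.3 | 43% | 61% | 36% |
| 0.5 | 36% | 51% | 31% |
| 0.7 | 28% | 39% | 24% |

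The first row agrees with step 4 within simulation error. Taking only 1 set against 3 sets, the two within-protocol verdicts disagree in about 16% (correlation 0.7, dz = 0.5) to 50% (correlation 0, dz = 0.33) of trials.

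**6. The direct contrast.** In the same simulated data, a paired t test of each woman's change with 1 set against her change with 3 sets is significant in 4.8% to 5.2% of trials in every cell, as it should be when the volumes do not differ.

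**The case against.** The strongest reply is that the plan already holds the right comparison. The sentence that plans within-group tests also plans the interaction and the between-group differences, the only named post hoc test is between groups, and 2.16 speaks of superiority of one program over another. This stands: the plan does not rely on within-group tests alone. What it lacks is any statement that the between-volume results govern the conclusion.

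A reader might infer that the authors intend to claim, say, that 1 set lowers pain and 3 sets does not. No passage announces such a conclusion. A reader might also infer that the design cannot show a difference in pain change between volumes. That is wrong: the randomised crossover compares 1, 2 and 3 sets directly. Only the absolute statement that a given volume changes pain lacks a comparator.

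The illustration is also open to challenge. Its inputs are assumed, and 75% is close to the maximum of the formula, which peaks at p = 0.5; with independent sessions and p at 5% or 95%, mixed verdicts fall to about 14%. A mixed pattern becomes an error only if someone reads it as a difference. The 5% belongs to a direct paired contrast, not to the planned mixed ANOVA, which treats group as varying between subjects although each woman performs every protocol. These limits stand, and the figures are offered only as an illustration.

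Finally, 2.18 defines time by visit (T0 to T4), so the exact meaning of a within-group difference is not settled. But each woman performs each protocol at a single visit, so the repeated ratings taken during a protocol are those before, after and at 24 h. That is the natural reading, and the lack of a comparator does not depend on it. A separate analysis plan might rank the contrasts. The tests themselves are stated here, on an equal footing.

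**Conclusion.** The point holds in a limited form. The article plans significance tests on an uncontrolled contrast and places them level with the randomised comparisons. For pain and affect, a change within one protocol cannot be attributed to training, and separate p-values for 1, 2 and 3 sets do not show whether volumes differ. Under the assumed conditions, with no true difference between volumes, within-protocol verdicts are mixed in about 24% to 75% of trials, against about 5% for a direct paired contrast. The range depends on the assumed change and correlation; the reasoning does not. The sample size and the primary outcome are unaffected. This is a worthwhile, inexpensive improvement to the secondary analyses, not a flaw in the design.

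**What to change.** In 2.18, replace the sentence on interactions and group differences with wording such as:

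> Conclusions on secondary outcomes rest on within-woman contrasts between 1, 2 and 3 sets, or on the volume × time interaction where an outcome is rated repeatedly in a session, each with a 95% confidence interval. Changes in pain and affect within a protocol are descriptive, shown as means with intervals, and are not attributed to training.

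The presentation to patients under 2.16 should follow the same rule. The cost is that some within-protocol p-values go unreported. No additional data, visits or participants are needed.

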## Results

3

Based on the design of this protocol, we intend to evaluate the preference of women with fibromyalgia in three different protocols in resistance training, evaluating these patients over 4 weeks where all of them will experience the three protocols. 7 days after the last week of the protocol, we will evaluate the patients' preference.

## Discussion

4

Although resistance training is recognized as a treatment for women with fibromyalgia, it is important to note that treatment for this population in Brazil is almost exclusively pharmacological; additionally, most people who exercise do aerobic exercises (Macfarlane et al. 2017; A. M.R. de et al. 2020). Therefore, patients with fibromyalgia in Brazil undergoing pharmacological and non‐pharmacological treatment do not receive complete treatment, as resistance training is not included (A. M.R. de et al. 2020).

The benefits of resistance training for patients with fibromyalgia are indisputable, such as: improvement in pain, function, quality of life, pain points, and improvement in physical fitness (Astley et al. 2021). However, we still observe a high abandonment of activities by these patients; some say that part of this situation is because of previous bad experiences with physical exercise and the beliefs of the patients (Russell et al. 2018).

It is plausible to assume that low adherence or abandonment of any type of treatment, in this case physical exercise, is not due to just one factor exclusively. It is very likely that this situation is materialized by multiple factors, such as: lack of patient education (Souza et al. 2008), lack of specialized care (Barton et al. 2021), lack of financial resources and educational background of the patient (A. T. R.C. de et al. 2017), the lack of willingness of the health professional to raise awareness among the patient and poor communication between the health professional and the patient can influence the prognosis and success of the treatment (Georgopoulou et al. 2018).

In contrast, although we recognize the complexity of non‐adherence and the real danger of a sedentary lifestyle for rheumatic patients regardless of age, we have observed an increasing number of studies in the literature that further reinforce the benefits of resistance training for patients with fibromyalgia (Rodríguez‐Domínguez et al. 2024), studies that investigate one of the acute variables of training, intensity (Rodríguez‐Almagro et al. 2023), and we have even observed studies that question modalities that were previously considered beneficial for patients with fibromyalgia (Pontes‐Silva, Dibai‐Filho, et al. 2023).

Importantly, distinguishing between prescribed and preferred exercise intensity can significantly impact the outcomes of resistance training for patients with fibromyalgia; da et al. (2018) demonstrated that patients reported lower pain perception during and after resistance exercise sessions performed at a preferred intensity compared to a prescribed intensity. Despite the fact that both intensities were matched in volume, the preferred intensity condition was associated with greater potential for adherence and more favorable affective responses. These findings underscore the importance of including resistance training in treatment plans and tailoring its variables, such as intensity, to patient preferences. This approach aims to minimize symptom exacerbation and increase adherence.

However, there are few studies that take into account the preference of the type of physical activity preferred by healthy individuals and especially by people with fibromyalgia (Pontes‐Silva 2024b). In addition, studies that have acknowledged the importance of patient preference in choosing exercise have shown superior outcomes in terms of adherence, symptom improvement, and physical fitness (Pontes‐Silva, Nunes, et al. 2023).

In addition to its physical benefits, considering exercise preference has been shown to improve psychological outcomes in individuals with fibromyalgia. For example, Andrade et al. (2020) found that patients who engaged in their preferred form of exercise reported better mental health indicators, including reduced symptoms of anxiety and depression, compared with patients who performed non‐preferred activities. These findings highlight the biopsychosocial nature of fibromyalgia and the importance of incorporating patient‐centered approaches into treatment planning. Allowing patients to choose exercise modalities or characteristics that align with their preferences may lead to more comprehensive, sustainable, and psychologically supportive interventions.

Therefore, in addition to the aforementioned reasons for the importance of incorporating patient preference into treatment planning, we also reiterate the pillars of evidence‐based practice, emphasizing that patient preference is part of the triad of this relevant behavior in clinical decision‐making by all health professionals (Garber et al. 2011).

One of the main strengths of this study is its focus on patient preference in relation to resistance training volume, a variable often overlooked in intervention designs. By directly evaluating this component, our protocol adheres to the clinical relevance of individualized treatment and the principles of evidence‐based practice. Furthermore, using three distinct resistance training volumes provides a comprehensive framework for detecting nuanced differences in patient preferences. This approach may enhance the ecological validity and applicability of our findings in real‐world clinical settings.

Another important strength of this research is its contextualization within the Brazilian healthcare system, where fibromyalgia treatment is predominantly pharmacological and access to comprehensive non‐pharmacological care is limited. By addressing these systemic challenges and proposing a low‐cost, scalable intervention, such as resistance training, our study offers a practical, culturally relevant contribution that could influence future policies and professional practices in other low‐ and middle‐income countries.

Nevertheless, some limitations should be considered. Since this is a protocol, the actual behavior of the patients, such as their adherence and preferences, will only be fully understood upon implementation. Additionally, our study is restricted to women, which may limit the generalizability of the findings to men with fibromyalgia. Additionally, while we examined an important acute variable, training volume, we standardized other parameters, such as intensity, frequency, and exercise modality, which could influence patient experience and perceived preference.

Despite its limitations, this study is novel in its patient‐centered approach and specific focus on training volume preference, an understudied aspect of fibromyalgia management. While the literature extensively covers the effectiveness and safety of exercise interventions, few studies have investigated which training characteristic patients prefer. Our clinical trial protocol fills this gap by providing new insights that may help design more acceptable, sustainable, and individualized exercise programs for women with fibromyalgia. It also serves as a basis for future studies in rheumatology and exercise science.

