### Sample Size

2.17

Sample size calculation was performed a priori using G*Power software (version 3.1.9.7) with the Chi‐squared test for comparisons between the proportions of self‐reported preferences observed in the contingency tables. We calculated the sample seeking an effect size of 0.8 in the difference in the primary outcome (preference). That is, *w* = 0.8, α = 0.05, β = 0.80, degrees of freedom = 25, non‐centrality parameter λ = 23.04, and critical Chi‐squared test = 37.65 (Gignac and Szodorai 2016; Pontes‐Silva 2023). Thus, the sample was estimated to be 36 patients.

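### With the three-way choice tested on 2 df, 36 women give 80% power only at w of about 0.52, so section 2.17 misstates the detectable effect and the Discussion's claim to detect nuanced differences is unsupported

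*Protocol article*

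**What the plan says.** - **Protocol article, 2.17 Sample Size.** The effect size is given as "We calculated the sample seeking an effect size of 0.8 in the difference in the primary outcome (preference"). The other inputs are "α = 0.05, β = 0.80, degrees of freedom = 25, non‐centrality parameter λ = 23.04, and critical Chi‐squared test = 37.65", and the result is "Thus, the sample was estimated to be 36 patients". The β of 0.80 is evidently the power.
- **Protocol article, 2.18 Statistical Methods.** For the primary outcome, "the number of choices of the 3 types of training will be recorded as a percentage". The planned analysis is to "summarize the patient's preference in a contingency table, compare the proportions using the chi‐squared test, and finally verify the effect size of the observed differences". No null proportions are given.
- **Protocol article, 2.6 Intervention and Comparator.** At T4 each woman is asked which of the programmes with 1, 2 or 3 sets she preferred, so each contributes one choice out of three.
- **Protocol article, 4 Discussion, strengths.** "using three distinct resistance training volumes provides a comprehensive framework for detecting nuanced differences in patient preferences". The limitations that follow do not mention sensitivity to smaller differences in preference.

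**The concern.** An effect size of w = 0.8 is very large for a choice among three options. If the other two protocols share the remainder equally, it means about 71% of women choosing one protocol. A trial sized on that effect does not sit easily with a claim to detect nuanced differences. The degrees of freedom also do not fit the outcome, so section 2.17 does not tell the reader what 36 women can in fact detect.

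What is at stake is how a non-significant primary test is read. Suppose 18 of 36 women choose one protocol and 9 choose each of the others. The leading protocol has twice the support of either rival, yet chi-squared is (6² + 3² + 3²)/12 = 4.5 on 2 df, p = 0.105. A reader who has been told that the design picks up nuance could take that as evidence of no preferred volume, and so as evidence against the trial's hypothesis that lower volumes are preferred.

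**Working it through.** **Inputs.** From section 2.17: w = 0.8, α = 0.05, power 0.80, df = 25, λ = 23.04, critical value 37.65, N = 36. From sections 2.6 and 2.18: three response categories, one choice per woman, chi-squared test. Assumptions: null shares of one third each, and all 36 women state a preference.

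**Step 1. Reproduce the plan's figure.** λ = N·w² = 36 × 0.64 = 23.04. The 95% point of chi-squared on 25 df is 37.65. The non-central chi-squared (25 df, λ = 23.04) exceeds it with probability 80.4%; with N = 35 the power is 78.9%. The printed 36 is reproduced with df = 25.

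**Step 2. Use the test that fits the outcome.** Three categories against fixed equal shares give df = 3 − 1 = 2, critical value 5.991.
- At w = 0.8 and N = 36, power is 99.4%.
- At w = 0.8, 80% power needs only 16 women.
- 80% power on 2 df needs λ of about 9.63, so with 36 women the detectable w is √(9.63/36) = 0.517.

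**Step 3. Translate w into shares.** With null shares of 1/3, w² = 3·Σ(pᵢ − 1/3)². If one protocol has share p and the other two are equal, this becomes w² = 4.5·(p − 1/3)².
- w = 0.8: p = 1/3 + 0.8/√4.5 = 0.710, that is 71/14.5/14.5.
- w = 0.517: p = 1/3 + 0.517/√4.5 = 0.577, that is about 58/21/21.

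**Step 4. Power at N = 36 on 2 df.** The exact column sums multinomial probabilities over all outcomes with chi-squared of at least 5.991.

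| True split (%) | w | Approximate power | Exact power |
|---|---|---|---|
| 40/30/30 | 0.14 | 11% | 12% |
| 40/35/25 | 0.19 | 16% | 17% |
| 45/30/25 | 0.25 | 26% | 28% |
| 50/25/25 | 0.35 | 46% | 48% |
| 50/30/20 | 0.37 | 51% | 54% |
| 55/22.5/22.5 | 0.46 | 69% | 71% |
| 55/30/15 | 0.49 | 76% | 80% |
| 58/21/21 | 0.52 | 81% | 81% |
| 60/20/20 | 0.57 | 87% | 87% |
| 71/14.5/14.5 | 0.80 | 99% | 99% |

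The exact figures are slightly favourable, because with 36 women the test rejects 6.0% of the time under equal shares.

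**Step 5. Is there one leading share that marks the limit?** No. When one option is rarely chosen, a smaller leading share is enough: exact power is 90% at 50/40/10 and 89% at 45/45/10 (w of about 0.51 and 0.49). At 50/25/25 the leading share is also 50%, yet power is 48%.

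**Step 6. Size needed for smaller effects.** On 2 df, 80% power for 50/25/25 needs 78 women, and for w = 0.3 it needs 108.

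**The case against.** The strongest reply is that the Discussion sentence makes no power claim. Its subject is the use of three graded volumes, it gives no effect size or sample size, and it governs no analysis. That largely stands: the sentence is qualitative, and the figure that needs correcting is in section 2.17. Still, a capacity to detect differences is a statement about sensitivity, it is offered as a strength, and nothing in the article supports it at this sample size.

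A second reply is that section 2.18 already promises percentages, an effect size and 95% confidence intervals, so a reader would not depend on the p-value alone. That stands too, and no separate request for intervals is needed.

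Two stronger readings are tempting, and the documents do not support either.
- A reader might infer that 71% is the trial's limit of detection because it was sized on w = 0.8. It is not. The 36 comes from using 25 df; on 2 df the same 36 women have 99% power at that effect.
- A reader might infer that moderate preferences will usually be missed. The article defines no moderate preference, and the figures do not bear this out in general: power is 54% at 50/30/20, 71% at 55/22.5/22.5 and 87% at 60/20/20. Missed more often than not is true for weaker splits such as 45/30/25, and narrowly so at 50/25/25.

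**Conclusion.** The point holds as a minor correction. Section 2.17 gives a detectable effect that does not belong to the planned comparison. For a single choice among three protocols, the 80%-power effect with 36 women is w of about 0.52, not 0.8. The trial is thus more sensitive than its own sample size statement says. It is still not sensitive to subtle differences: exact power is 12% to 17% when the leading protocol has 40%, 28% at 45/30/25, and about an even chance at 50/25/25 or 50/30/20. The word *nuanced* is not supported.

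This rests on an equal-share null, which the article does not state, and on a preference from all 36 women; any loss would lower the power. Under the article's own 25 df the claim would fare worse (16% at 50/25/25, 42% at 60/20/20), so the conclusion about *nuanced* does not depend on which df is used.

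**What to change.** 1. **Section 2.17.** Replace the statement based on w = 0.8 and 25 df with one on the planned test, and name the null. For example:

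> Against equal preference for the three protocols (2 df, α = 0.05), 36 patients give 80% power for w of about 0.52, for example a 58/21/21 split.

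2. **Discussion.** Either drop *nuanced*, or say that only large departures from equal preference (w of about 0.5 or more) are reliably detectable and that a non-significant test is inconclusive for smaller ones.

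3. **Avoid a leading-share threshold.** Wording such as one protocol chosen by 58% or more would bring in a new error, because power depends on how all three shares are distributed. Give w, and splits only as examples.

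The cost is a few sentences. No patients, visits or analyses are added, and the corrected detectable effect in section 2.17 is smaller than the one now printed. Only the Discussion's description of the design's sensitivity becomes more modest.
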